##### Attachment

Because of the explicitly interpersonal nature of the intervention, both in the form of the face-to-face sessions, and the use of peer material, attachment style is included as a potential moderator. This is measured by the Psychosis Attachment Measure [74], a brief 16-item self-report questionnaire designed to assess avoidant and anxious attachment styles in persons with psychotic disorders.

##### Cognitive function

To determine whether cognitive function limits ability to benefit from resources, the WTAR will be used to control for premorbid IQ, in combination with tests of current cognitive functioning. The WTAR is administered as a test of premorbid IQ where participants are asked to read a list of 50 words that have atypical grapheme to phoneme translations (e.g., “liaison”, “ paradigm”) and are scored according to accuracy of pronunciation (raw score range 0–50). WTAR raw scores are standardised based on age then converted to the predicted WAIS-III IQ. While predicted IQ scores will be reported descriptively, these are associated with very large confidence intervals; standardised scores will therefore be used for analyses due to their greater precision. A small battery of cognitive functioning tests will additionally be administered. These include *Digit Symbol Coding* [76]*, Animal Fluency, Trails A and B* [76]*, Digits Forward and Digits Backward*. These tests assess the cognitive domains of executive function, verbal working memory, cognitive processing speed, task-switching and visual attention. Each assessment involves completion of paper and pencil cognitive assessments which are among the most frequently used in research and clinical practice and are well standardised with accepted norms. The battery takes a total of 8–10 min to complete. Each task will be briefly described below:

*Digit Symbol Coding* [75]*:* Participants are asked to use a key to write the numbers in a grid that correspond to nonsense symbols over a 90 s period. The total number of correct responses in used as the performance measure.

*Animal Fluency:* Participants are asked to give the names of as many animals as they can think of within a one-minute period. The number of unique animals produced is used as the primary performance measure, with repetitive errors or perseverations also noted.

*Trails A and B* [76]: For part A the participant is required to connect a series of 25 numbers in a circle as quickly as possible. They are asked to connect them in sequential order as quickly as possible without removing their pencil from the page. In part B the participant alternates between numbers and letters (i.e. 1, A, 2, B etc.). If the participant makes an error the experimenter corrects them before they move to the next circle. The time taken to complete each part is used as the performance metric.

*Digits Forward and Digits Backward:* For the forward condition participants are presented with lists of digits and must immediately repeat them. The length of the list increases on each trial. Participants are given two versions of each list length and score 1 point for each. After failing both versions of a list length the task is terminated. The total score is then calculated. For the backward condition, the participants need to reverse the order of the numbers.

Each of the primary variables for each task will be standardised based on age: Using these standardised scores a global mean current cognitive performance score will be calculated and used as a covariate in the analyses.

##### Intervention engagement/dose

Number of sessions attended and amount of time spent on each session will be recorded. In the SMART condition, access of the online materials using the participant’s username will be recorded automatically and usage within sessions and outside of sessions recorded.

##### Receipt of other treatments

Antipsychotic medication doses and receipt of psychological treatment will be tracked at each assessment point. These will be compared between groups, and to exclude these as accounting for outcomes, their relationship with outcome will be examined (medication doses converted into chlorpromazine equivalents).

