### Design

The SMART-Therapy trial is designed as a randomised, controlled, assessor-blinded superiority trial, with two parallel groups, using a 1:1 allocation ratio. The two groups both receive eight sessions with a mental health worker in addition to their routine care during a three month window, with one group being delivered the recovery intervention, and the other being delivered a befriending intervention as a comparison condition. Outcome measures are completed at baseline (prior to randomisation) and are repeated at 3, 6 and 9 months following baseline.

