### Participants

The study is being conducted across multiple public community mental health services in the state of Victoria, Australia, including clinical mental health services, and not-for-profit organisation-run community mental health support services. Potential participants are identified via referral from practitioners in collaborating services, supplemented by review of case-lists, plus advertising within services, and in print and online social media.

Inclusion criteria are: (a) age between 18 and 65 years inclusive; (b) diagnosis of a nonorganic psychotic disorder (schizophrenia-related disorder or bipolar disorder or major depressive disorder with psychotic features present within the past 2 years), confirmed using the Structured Clinical Interview for DSM-IV-TR Axis I Disorders (SCID) [49]; (c) sufficient conversational English for meaningful participation; (d) overall intellectual functioning within normal limits (having an IQ greater than 70, as estimated by the Wechsler Test of Adult Reading (WTAR) [50]) to ensure they have the cognitive capacity to provide consent, in addition to being able to adequately engage with the intervention. Exclusion criteria are: (e) initiation of a new antipsychotic medication, or commencement or completion of a formal psychological treatment, within the previous 8 weeks; (f) inpatient admission within the previous 8 weeks.

The recruitment target is 148 participants, providing 80 % power to detect medium effect sizes (*d* = 0.5) at α = .05 with 15 % attrition. This was based on an average effect size of *d* = 0.53 observed in a meta-analysis of online interventions [51].

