### Measures

A schedule of assessments is provided in Table 1. Assessments are performed as close as possible to the allocated time-point. If the assessment cannot be performed within 6 weeks of the allocated time, this assessment is considered missed and the next assessment is performed at the allocated time.

**Table 1 Tab1:** Participant timeline

	Study period					
	Enrolment	Allocation	Post-allocation			Close-out
Timepoint	Baseline		Week 1–12	3 months	6 months	9 months
	(*t* _0_)					
Enrolment						
Eligibility screen	X					
Informed consent	X					
Allocation		X				
Interventions						
SMART			X			
Befriending			X			
Assessments						
QPR	X			X	X	X
Schizophrenia Hope Scale	X			X	X	X
UCLA Loneliness Scale	X			X	X	X
PANSS	X			X	X	X
SEPS	X			X	X	X
DASS-21	X			X	X	X
AQoL8D	X			X	X	X
STAR-Patient	X			X	X	X
Therapy Evaluation				X		
Serious Adverse Events	X		X	X	X	X
RUQ	X			X	X	X
ISMI	X			X	X	X
Self-efficacy measures	X			X	X	X
Demographics	X					
SCID	X					
Internet Use and Access	X			X	X	X
Recovery Style Questionnaire	X			X	X	X
Peer Identification Scale	X			X	X	X
Psychosis Attachment Measure	X			X	X	X
WTAR	X					
Cognitive tests	X					
Engagement measures			X	X	X	X
Medication and psychological treatment	X			X	X	X
Expectancy Scale			X			

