The differential effects on outcomes of the process variables (self-efficacy and self-stigma) and medication changes will be tested across conditions with a maximum likelihood Hierarchical Linear Modelling analysis. In these models time will be treated as a linear covariate. Baseline measures for cognitive function, recovery style, intervention engagement, diagnosis, demographics, baseline internet use and expectancy will be used as covariates, while testing interaction effects for condition and the baseline social engagement moderators (loneliness, attachment, peer group identification and peer contact). Structural equation modelling will then be used to demonstrate the mediation mechanism of outcome improvement for each condition separately, with bootstrap analyses used to obtain 95 % confidence intervals for all effect sizes.

Data will also be used as part of a broader economic evaluation of the use of the website involving cost-consequences analyses whereby incremental costs of interventions using the site are compared with the full spectrum of outcomes measured vs relevant comparators. For this study, QALYs will be calculated from AQoL8D data, and costs will be derived from estimates of the costs involved in running the website (website development and maintenance costs, forum moderation, and therapist activity data), adjusted for any differences in resource use between conditions. Standardised economic evaluation techniques will be used including incremental analysis of mean differences, with confidence intervals derived using bootstrapping.

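### Relating post-randomisation antipsychotic dose and psychological treatment to outcome cannot exclude co-treatment as an explanation; the planned between-arm comparison should carry that statement

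*Protocol article*

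**What the plan says.** In the protocol article, Receipt of other treatments states: "Antipsychotic medication doses and receipt of psychological treatment will be tracked at each assessment point". Two uses follow. The first is a comparison of the two arms. The second reads: "to exclude these as accounting for outcomes, their relationship with outcome will be examined (medication doses converted into chlorpromazine equivalents").

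The section on analysis of the data carries medication into a model. Alongside the process variables (self-efficacy and self-stigma), the effects of "medication changes will be tested across conditions with a maximum likelihood Hierarchical Linear Modelling analysis", with time as a linear covariate. The primary analysis, described earlier in the same section, is a mixed model for repeated measures with no medication term.

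Three other places bear on the point:

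- Participants admits people with "schizophrenia-related disorder or bipolar disorder or major depressive disorder with psychotic features present within the past 2 years".
- Interventions says that usual care continues under the existing treating team, unrestricted by the trial, and may include formal psychological therapy.
- Table 1 (Measures) has a row headed "Medication and psychological treatment", marked at baseline and at 3, 6 and 9 months, with no limit to antipsychotics.

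**The concern.** The text states a purpose, which is to exclude co-treatment as the reason for the results, and an analysis, which is the relationship between co-treatment and outcome. The analysis cannot serve the purpose. Randomisation protects the comparison of arms. It does not protect a comparison of people on higher and lower doses after randomisation. Treating teams are free to change treatment during follow-up and may do so because someone is doing better or worse. A treatment that helps can then show no association with outcome, and a treatment that does nothing can show a strong one.

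The second part is coverage. Chlorpromazine equivalents express antipsychotic dose only. A participant who qualifies through "bipolar disorder or major depressive disorder with psychotic features present within the past 2 years" may have an antidepressant or mood stabiliser changed, and on this scale that counts as no change. Such changes could plausibly bear on the depression, anxiety and stress scores (DASS-21), which are secondary outcomes.

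At stake is a sentence in the results paper saying that medication and other therapy have been ruled out, in either direction, on evidence that cannot show it.

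**Working it through.** **The plan's own figure.** The only figure nearby is the sample size: "The recruitment target is 148 participants, providing 80 % power to detect medium effect sizes (*d* = 0.5) at α = .05 with 15 % attrition", "using a 1:1 allocation ratio". With a two-sided test (assumed; sidedness is not stated), the normal approximation gives 63 per arm, 126 in total, and 126 / 0.85 = 148.2. The target reproduces. The point does not depend on it; 126 is used below as the number evaluable.

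**Step 1: an association when dose has no effect.** Let outcome Y = τT + e, with T the arm, τ = 0.50 and e of unit variance. Let dose respond to outcome and do nothing itself: M = −rY + √(1 − r²)·u, with u of unit variance. Within an arm M has variance r² + (1 − r²) = 1 and its correlation with Y is −r.

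Regress Y on T and M. The coefficient of M is −r. The arms differ in mean dose by −rτ. The coefficient of T is therefore τ − (−r)(−rτ) = τ(1 − r²).

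Simulation with 126 evaluable, 4,000 runs, one follow-up time and a 5% test of dose:

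| assumed r | unadjusted effect | effect adjusted for dose | τ(1 − r²) | dose 'significant' |
|---|---|---|---|---|
| 0 | 0.498 | 0.498 | 0.500 | 4.6% |
| 0.2 | 0.499 | 0.479 | 0.480 | 61.9% |
| 0.3 | 0.503 | 0.458 | 0.455 | 93.2% |
| 0.5 | 0.500 | 0.376 | 0.375 | 100% |

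The values of r are assumptions; the documents give none. At r = 0 there is no distortion. At r = 0.2 an inert dose is already flagged in most trials.

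**Step 2: no association when dose does have an effect.** Let S be illness severity, with M = aS + u and Y = bM − cS + e, where a, b and c are positive and S and M are scaled to unit variance. The slope of Y on M is b − ac. When b = ac it is zero although dose helps; when b < ac it is negative. A null or inverse association therefore does not show that medication played no part.

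**Step 3: treatment outside the described measure.** The unseen shift in the overall arm difference is (share with a mood disorder) × (arm difference in starting such a drug) × (drug effect). None of these is in the documents. Assume a share of 10% to 30%, an arm difference of 20 to 40 percentage points within that group, and an effect of 0.5 SD:

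- low: 0.10 × 0.20 × 0.5 = 0.01 SD
- high: 0.30 × 0.40 × 0.5 = 0.06 SD

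Both are small beside the design effect of 0.5.

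**Step 4: the sections side by side.** Receipt of other treatments names antipsychotic doses; Table 1 names medication. The first describes a narrower record than the second allows. The data forms are not shown, so the article does not settle which applies.

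**The case against.** The strongest reply is that the check is supportive and that its sound half is already planned. The sentence that speaks of exclusion begins with a between-group comparison of the same treatments. Randomisation protects that comparison, and it is the right basis for asking whether the arms were treated differently. This stands, and the fix builds on it. It does not rescue the second half of the sentence. A non-significant between-arm difference would not prove equality either.

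Three stronger readings are tempting, and the documents support none of them.

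- *The trial's main result is biased by up to a quarter.* The reductions in Step 1 (9% at r = 0.3, 25% at r = 0.5) arise only if the SMART effect is read from a model containing post-randomisation dose. The primary model contains no such term, and the article does not say that the effect will be read from the hierarchical model.
- *Outcome drives dose.* Unrestricted care makes this possible, but the article does not state it. It is more plausible for PANSS symptoms than for the primary outcome, the QPR, which is a self-report of personal recovery that the Background contrasts with symptom reduction.
- *Antidepressants and mood stabilisers are not measured.* The Table 1 row is unrestricted and this is a condensed article. One can say only that such recording is not described.

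**Conclusion.** The point holds in a limited form. An association between co-treatment after randomisation and outcome is observational, so neither its presence nor its absence can exclude co-treatment as an explanation. This needs only the timing in Table 1 and the unrestricted care described under Interventions. It does not require that outcome in fact drives dose, only that the design leaves this open.

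The described measure is narrower than the enrolled population. Whether the actual record is narrower too is unresolved.

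The consequence is confined to the supportive conclusion about medication and psychological treatment. The primary intention-to-treat comparison is untouched. The shrinkage to 0.46 or 0.38 SD and the unseen shift of 0.01 to 0.06 SD are illustrations under assumed inputs, not estimates for this trial.

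**What to change.** 1. Base any statement about co-treatment on the between-arm comparison already planned. Report each difference with a confidence interval; do not treat a non-significant test as evidence of equality.
2. Reconcile Receipt of other treatments with Table 1 by stating which drug classes the medication record holds. Extend the between-arm comparison to antidepressant and mood-stabiliser use from that record.
3. Label the dose-outcome analysis and the medication-change model exploratory. State that the SMART effect will not be read from a model adjusted for post-randomisation dose.
4. Delete the claim that these analyses exclude co-treatment.

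An analysis that sets the QPR to missing once a new treatment starts may look like an alternative, but it should not be used. It conditions on a post-randomisation event that may follow deterioration, so it repeats the same fault.

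The cost is a few sentences and some extra rows in a table. The downside is that the trial was registered during recruitment, so if other drug classes were not recorded from the start, the data may be incomplete for participants already assessed. That should be reported. The paper would also make a more modest claim about medication.

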### Data analysis

Data are initially recorded on paper forms which are securely stored and extracted into password protected electronic files. Data extraction is conducted by research staff blind to participant allocation. Procedures to identify potential errors include double entry from selected paper files, range checks, and examination of outliers.

The primary focus of the analysis is differential changes in the SMART group versus Befriending over the full post intervention period. Analyses will be undertaken using mixed-model repeated measures (MMRM) allowing for autoregressive dependence. MMRM is well-suited to ITT analyses because this approach uses all available information from subjects. Participants with incomplete data are not discarded and missing data are not replaced with estimated values or observations carried forward. Instead maximum-likelihood estimation is applied with the available data. Where there are significant group x time interactions, planned contrasts will compare changes from baseline under each intervention.

Where outcome measures exhibit non-normal distributions across time points, appropriate transformations will be applied. If any of the outcome measures show significant baseline differences between SMART and Befriending, and between completers and noncompleters, corrections for sample imbalance and attrition bias will be applied using propensity scoring. This will involve firstly constructing a logistic regression model with treatment condition as the outcome, and baseline clinical variables and demographics as predictors, plus a “missing-at-post-therapy” variable to index differential effects of attrition. Secondly the effects of any imbalance or attrition will be addressed by including the estimated probabilities from this model (propensity scores) as a covariate in analyses.

The differential effects on outcomes of the process variables (self-efficacy and self-stigma) and medication changes will be tested across conditions with a maximum likelihood Hierarchical Linear Modelling analysis. In these models time will be treated as a linear covariate. Baseline measures for cognitive function, recovery style, intervention engagement, diagnosis, demographics, baseline internet use and expectancy will be used as covariates, while testing interaction effects for condition and the baseline social engagement moderators (loneliness, attachment, peer group identification and peer contact). Structural equation modelling will then be used to demonstrate the mediation mechanism of outcome improvement for each condition separately, with bootstrap analyses used to obtain 95 % confidence intervals for all effect sizes.

Data will also be used as part of a broader economic evaluation of the use of the website involving cost-consequences analyses whereby incremental costs of interventions using the site are compared with the full spectrum of outcomes measured vs relevant comparators. For this study, QALYs will be calculated from AQoL8D data, and costs will be derived from estimates of the costs involved in running the website (website development and maintenance costs, forum moderation, and therapist activity data), adjusted for any differences in resource use between conditions. Standardised economic evaluation techniques will be used including incremental analysis of mean differences, with confidence intervals derived using bootstrapping.

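### If the autoregressive covariance is first-order with no subject random effect, it makes the later change-from-baseline standard errors too large when stable person-level differences persist; an unstructured matrix avoids this at little cost

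*Protocol article*

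**What the plan says.** Under Data analysis, the protocol article names one dependence structure for its repeated-measures model: "Analyses will be undertaken using mixed-model repeated measures (MMRM) allowing for autoregressive dependence". The model is fitted to incomplete data without imputation: "Instead maximum-likelihood estimation is applied with the available data". The stated focus is "differential changes in the SMART group versus Befriending over the full post intervention period", and where the group-by-time interaction is significant, "planned contrasts will compare changes from baseline under each intervention". Baseline is therefore one of the modelled time points.

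Under Design, the visits are equally spaced: "Outcome measures are completed at baseline (prior to randomisation) and are repeated at 3, 6 and 9 months following baseline". Under Participants, the target is 148, "providing 80 % power to detect medium effect sizes" of d = 0.5 at α = .05 with 15% attrition.

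The article does not state the order of the autoregression, whether a subject random effect is added, or any within-person correlation for the Process of Recovery Questionnaire (QPR).

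**The concern.** A first-order autoregressive structure ties every longer-lag correlation to the 3-month one: ρ at 3 months, ρ² at 6 and ρ³ at 9. It leaves no room for a part of the score that stays with the person. The trial enrols people with persisting psychosis, and its primary outcome is a self-report total, so a lasting person-level component is plausible, although the article does not quantify it.

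If such a component exists, the model understates how strongly the 6- and 9-month scores relate to baseline. The variance of a change score is 2σ²(1 − correlation), so an understated correlation means an overstated standard error. The contrasts affected are the later and averaged changes, which are central to an analysis focused on the whole post-intervention period. At stake are over-wide intervals and lost power.

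**Working it through.** **Reproducing the sample size.** Per arm: 2 × (1.960 + 0.842)² / 0.5² = 62.8, rounded up to 63, or 126 in total. Then 126 / 0.85 = 148.2, which agrees with the stated 148. After attrition, 148 × 0.85 = 125.8, or 62.9 per arm, with power 80.1% (normal approximation, two-sided). This figure is sound, and the point does not change it.

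**What first-order autoregression forces.** A 3-month correlation of 0.5, 0.6 or 0.7 gives a baseline-to-9-month correlation of 0.125, 0.216 or 0.343.

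**Assumed true structures.** Because the article gives no QPR correlations, a range was used, with unit variance at every visit: (a) true first-order autoregression; (b) a person share p of the variance plus an autoregressive residual with parameter 0.5; (c) a constant correlation. For each true covariance C, the first-order form V was fitted by minimising log|V| + tr(V⁻¹C), the large-sample likelihood fit. In every case the fit returned variance 1 and ρ equal to the true 3-month correlation. For a contrast c, the ratio of model to true standard error is √(c′Vc / c′Cc). The ratio is the same for a within-arm change and for the difference in change between arms.

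**Worked case, constant 0.6, change to 9 months.**
- True variance: 2(1 − 0.6) = 0.800. Model variance: 2(1 − 0.216) = 1.568. Ratio: √(1.568 / 0.800) = 1.40.
- Between-arm standard error at 62.9 per arm: true √(2 × 0.800 / 62.9) = 0.1595; model √(2 × 1.568 / 62.9) = 0.2233.
- Power at a difference of 0.5 SD: with the correct standard error, Φ(0.5/0.1595 − 1.96) = 88%; with the model standard error, Φ((0.5 − 1.96 × 0.2233)/0.1595) = 65%.
- True size of the nominal 5% test: 2 × [1 − Φ(1.96 × 1.40)] = 0.6%.

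**Worked case, person share 0.5 plus AR 0.5.** The true 9-month correlation is 0.5 + 0.5 × 0.125 = 0.5625. The 3-month correlation is 0.75, and its cube is 0.422. Ratio: √(0.578 / 0.4375) = 1.15.

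**All cases** (complete data, 0.5 SD at each post-baseline visit; power is autoregressive versus correct standard error):

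| Assumed truth | SE ratio, 9 months | Size, 9 months | Power, 9 months | Power, average change |
|---|---|---|---|---|
| AR(1), ρ = 0.6 | 1.00 | 5.0% | 61% vs 61% | 84% vs 84% |
| Person 0.3 + AR 0.5 | 1.09 | 3.3% | 66% vs 72% | 89% vs 91% |
| Person 0.5 + AR 0.5 | 1.15 | 2.4% | 77% vs 85% | 96% vs 98% |
| Constant 0.5 | 1.32 | 0.95% | 58% vs 80% | 84% vs 93% |
| Constant 0.6 | 1.40 | 0.61% | 65% vs 88% | 90% vs 97% |
| Constant 0.7 | 1.48 | 0.37% | 76% vs 95% | 96% vs 99% |

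The 3-month ratio is 1.00 throughout. At constant 0.5 / 0.6 / 0.7, the 6-month ratio is 1.22 / 1.26 / 1.30 and the average-change ratio 1.24 / 1.30 / 1.35. Under the null, the 3-df group-by-time test that precedes the contrasts keeps a size of 4.1% to 4.8% in the cases with a persisting person component. Its power at the same sustained effect is 84% vs 86% and 94% vs 95% in the two mixed cases, and 70% vs 83% and 79% vs 91% at constant 0.5 and 0.6.

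**The case against.** The strongest reply is that the article only allows for autoregressive dependence. That wording also fits a subject random intercept with an autoregressive residual, which would largely remove the problem, and a condensed article may leave such detail to its analysis plan. This stands in part: the order is not stated, so the finding is conditional. But autoregression is the only structure named, and a better choice can be written in its place.

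The second reply is that the size is entirely assumed. That stands. A constant correlation over nine months is the opposite extreme from autoregression. The mixed cases give 9-month ratios of only 1.09 to 1.15, and the ratio is 1.00 if first-order autoregression is true.

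Three stronger readings are tempting, and none is supported.
- *The trial loses its planned power.* A contrast rescaled to have exactly 80% power would fall to about 52% at a ratio of 1.40, but that is not this trial's power. At the protocol's own d = 0.5 and about 63 per arm, the average-change contrast stays above 80% in every case examined.
- *False positives are inflated.* Every affected change contrast is conservative, and the interaction test is near nominal. A plain post-baseline mean that ignores baseline would have a ratio of 0.96 to 0.99 (size 5.2% to 6.1%), but the article specifies changes from baseline.
- *The handling of missing data fails.* Likelihood methods under dropout do rely on an adequate covariance, but all the calculations here use complete data, so no size can be put on this.

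**Conclusion.** The point holds in conditional form, as an inexpensive improvement. If the structure is first-order autoregressive without a subject random effect, and stable person-level differences persist, the 6-month, 9-month and averaged change contrasts have standard errors that are too large. The loss at 9 months runs from nothing (true autoregression), through 6 to 8 percentage points of power (person share 0.3 to 0.5), to about 23 points (constant 0.6). For the averaged change it is smaller: 84–96% instead of 91–98% across the two mixed cases and constant 0.5 to 0.6. The 3-month contrast and the recruitment target of 148 are unaffected.

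This rests on assumed correlations, equal variances across visits, complete data and a sustained 0.5 SD effect. The algebra is exact for first-order autoregression on equally spaced visits. Whether the condition applies, and how strongly, cannot be settled from the article.

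**What to change.** In Data analysis, replace the autoregressive specification with an unstructured covariance across the four visits. State the fallback if it does not converge: a random intercept plus first-order autoregressive residual, or robust standard errors.

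Cost: one sentence and no extra data. An unstructured matrix for four visits has 4 × 5 / 2 = 10 parameters, against 2 (one variance, one correlation) for the first-order form. Eight more parameters are affordable with 148 participants. If the true structure is first-order autoregressive, little is lost by estimating them.
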